### Study participants

Home-based BP testing using automatic BP machines has been initiated by AMPATH in both the Kosirai and Turbo divisions, with a plan to cover one-third of each community unit’s adult population every year. Inclusion criteria for this study will be all adult individuals with elevated BP (SBP >140 or diastolic BP (DBP) >90) during home-based testing, who will be assigned a unique medical record number and referred to the local dispensary for further evaluation (Figure 3). Exclusion criteria will be individuals without elevated BP, those who are acutely ill and require immediate medical attention at the time of testing, and individuals who do not provide informed consent. Enrollment will occur for one year in each unit.

**Figure 3 F3:**
[figure not shown]
**Classification of participants in trial.** BP = Blood Pressure; CHW-S = usual care arm; CHW-B = tailored behavioral communication strategy arm; CHW-BT = communication strategy and smartphone technology arm; CU- Community Unit.

An individual who does not present to the dispensary within one month will be defined as ‘non-linked’ and will be identified by the dispensary nurse. At that point in time, a CHW will be assigned to visit that individual to encourage linkage to care. Those who do not link to care within one month of the second CHW visit will be considered ‘chronic non-linked’. Individuals who ultimately link to care will be characterized as ‘self-linked’ (linked on their own without CHW intervention) or ‘CHW-mediated linked’. At the dispensary, each individual who has linked will have a repeat BP measured, and those with repeat elevated BP will be entered into the hypertension management program as patients. Patients will be managed according to the AMPATH hypertension protocol that is derived from consensus guidelines for hypertension management, using drugs contained in the Kenyan national formulary [38-40]. Patients who miss a clinic appointment for more than one month will be considered ‘non-retained’. Patients who are retained in care will be defined as either ‘self-retained’ (retained on their own without CHW intervention) or ‘CHW-mediated retained’. An individual will be considered ‘lost to follow up’ if they does not return to the clinic for three months despite CHW visits. The 12-month follow up BP will be measured in the dispensary, in order to mimic real-world practice.

### Intervention and control

In the UC arm, the CHW will first measure the individual’s BP. If it is elevated (SBP >140 or DBP >90), the CHW will refer the individual to the dispensary for further evaluation and management, as per the usual care protocol.

In the TBCS arm, the CHW will measure the individual’s BP and then will engage in behavioral, clinical, and environmental assessments. Based on the behavioral assessment, the CHW will employ the communication strategy consisting of tailored behavioral and motivational messages, as described above. Depending on the severity of the clinical assessment, the CHW will either refer or accompany high-risk patients to the dispensary. The environmental assessment will evaluate socioeconomic barriers to care-seeking, and the CHW will provide this information to the nurses in the dispensary.

In the TBCS-ST arm, the CHW will conduct all assessments described above; however, s/he will also be equipped with a smartphone that has real-time decision support and data entry that is linked to the electronic health record. Thus, the smartphone will provide the tailored messaging and specific recommendations based on inputs from the assessments. The smartphone technology would allow for alternative messaging modalities, such as images and recordings (audio and visual), to ensure its applicability to a population speaking diverse languages and with different literacy levels. If a patient does successfully go to the dispensary for the linkage visit, this visit will be entered into the electronic health record and we will program the system to immediately send a positive reinforcement message to the CHW.

### Outcomes

The co-primary outcome measures will be: 1) documented linkage to care, defined as a confirmed dispensary visit within one month of either home-based testing (self-linked) or a CHW visit (CHW-mediated linked), and 2) one-year change in SBP among those with hypertension. Our ultimate goal is to implement an intention-to-treat comparison of change in SBP among confirmed hypertensive individuals. However, confirmation of hypertensive status requires at least two BP measurements, and this requires successful linkage to care (Figure 3). Hence, we have opted for the co-primary outcome approach. We will compare the proportion linked to care between the three study arms using conditional logistic regression. For the SBP outcome, we will implement an intention-to-treat comparison of change in SBP between the three study arms. For those who are not successfully linked to care, we will use imputed SBP values. Full details of our approach to imputation appear in Additional file 2.

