The smartphone version will be linked to the electronic health record and will have two functionalities: 1) ability to provide each CHW with an automatically updated list of individuals requiring follow up; and 2) the ability to provide real-time decision support based on the communication strategy, using data collected by the CHW during a patient encounter. The decision support will use branching logic and decision trees based on specific motivational messages, as well as simple clinical care algorithms appropriate for CHWs. The smartphone technology will allow for alternative messaging modalities, such as images and recordings (both audio and visual).

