### Cluster randomized controlled trial

We will conduct a cluster randomized controlled trial with three intervention arms: 1) usual care - CHWs with standard training on recruitment of individuals with any chronic condition (‘UC’); 2) CHWs with a tailored behavioral communication strategy (‘TBCS’); and 3) CHWs with a communication strategy who are also equipped with smartphone technology (‘TBCS-ST’). The unit of randomization will be the community unit, since randomization by CHW or patient would be at risk for contamination, as all CHWs and nearly all patients within one community unit are affiliated with the same dispensary. Randomization will be stratified by division, so that the 9 units of Kosirai will be randomized separately from the 15 units of Turbo. The units will be randomly allocated to one of the three intervention arms. The randomization process will be conducted centrally by biostatisticians at Brown University (Providence, United States). We will compare key variables (such as age, sex, severity of initial SBP, different treatment regimens, previous history of hypertension treatment, socioeconomic status, body mass index, physical activity, alcohol consumption, and tobacco use) to ensure balance among the randomized groups, and make adjustments in our treatment effect estimates as needed using logistic regression adjustment.

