### Statistical power

The study is powered on the linkage-to-care outcome in order to preserve the properties of randomization at the community unit level and avoid bias due to differential selection into care by the linkage intervention. In light of AMPATH’s pilot experience with home-based testing and linkage to hypertension care [10], we anticipate that the usual care arm will have 40% linkage (self-linked plus CHW-mediated linked). The study is powered to detect an absolute difference of 20% in percent linkage to care between each of the three treatment arms (expected 60% linkage in the TBCS arm and 80% linkage in the TBCS-ST arm). It is expected that 226 people will be referred to the dispensary per community unit per year, based on the following: 1) each community unit has a population of approximately 5,000; 2) 45.3% of the population is above the age of 20 [41]; 3) one-third of the population will be screened during the year; and 4) approximately 30% of adults will have an elevated SBP at the home-based testing [10].

Our power calculations set overall Type I error rate at 5% (alpha = 0.05), and use a Bonferroni correction to permit all pairwise comparisons between treatment arms. To account for cluster effects, we consider scenarios where intraclass correlation (ICC) ranges from 0 to 0.15 [42]. Plots demonstrating power for each of the pairwise treatment arm comparisons across different values of ICC reveal that our pairwise comparisons have over 80% power over a large range of ICC values (Figure 4).

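### The linkage co-primary sets no common end date from home testing, so whether an attendance counts depends on whether a CHW visit took place

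*Protocol article*

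**What the plan says.** All references are to the protocol article.

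- **Outcomes.** Linkage, the co-primary on which the study is powered, is "defined as a confirmed dispensary visit within one month of either home-based testing (self-linked) or a CHW visit (CHW-mediated linked"). The definition has two starting points and gives no last date counted from the home test.
- **Study participants, text after Figure 3.** Someone who has not presented by one month is identified by the dispensary nurse, and then: "At that point in time, a CHW will be assigned to visit that individual to encourage linkage to care". The trigger is the same in every arm, and no deadline is given for the visit. The label chronic non-linked is tied to a later point: "Those who do not link to care within one month of the second CHW visit will be considered" as such.
- **Facilitators and barriers to linkage and retention to hypertension care.** One of the two functions of the smartphone version is the "ability to provide each CHW with an automatically updated list of individuals requiring follow up". The smartphone belongs to the TBCS-ST arm only.
- **Statistical power.** The planning rates are: "we anticipate that the usual care arm will have 40% linkage (self-linked plus CHW-mediated linked"), with "expected 60% linkage in the TBCS arm and 80% linkage in the TBCS-ST arm".

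**The concern.** The second starting point, a CHW visit, occurs after randomisation. A person who receives no CHW visit has one month in which attendance can count. One visit makes it two months, and two visits make it up to three. Two people who attend on the same day after their home test can therefore be scored differently because a visit did or did not happen, even if the visit had no influence on the attendance.

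If visits are completed equally often in all arms, this costs some linkage in each arm and biases nothing. If they are completed more often in one arm, that arm also has more counted time, and the comparison mixes two things: more people attending, and more of the attendances being eligible to count. The follow-up list in the smartphone version is a plausible route to more completed visits in that arm.

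**Working it through.** **Inputs from the article.** Planned linkage is 40%, 60% and 80%. Expected referrals: "It is expected that 226 people will be referred to the dispensary per community unit per year". There are 9 + 15 = 24 community units, and alpha is 0.05 with a Bonferroni correction over three pairs (0.05/3 = 0.0167).

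**Assumptions, not in the article.** The monthly linkage probability p is identical in both arms and in every month. A share v of the people due a CHW visit receive it, and the visit does not change p. Allocation is equal, with 8 units per arm.

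**Reproducing the article's figure.** 5,000 × 0.453 × 1/3 × 0.30 = 226.5, against 226 stated. It reproduces.

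**Formulas for counted linkage.**

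- One restart: p + (1 − p)·v·p
- Two restarts: p + (1 − p)·v·p + (1 − p)²·v²·p

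Both are shown because the article does not say whether the home test is the first CHW visit. If it is, the second visit is the follow-up visit and there is one restart. If it is not, there are up to two.

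Example with p = 0.15, v = 0.5 and two restarts: 0.15 + 0.85 × 0.5 × 0.15 + 0.7225 × 0.25 × 0.15 = 0.241. With v = 0.9 it is 0.353.

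**Visit shares of 50% against 90%**

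| Restarts | p per month | 50% visited | 90% visited | Artefact (points) |
|---|---|---|---|---|
| One | 10% | 14.5% | 18.1% | 3.6 |
| One | 15% | 21.4% | 26.5% | 5.1 |
| One | 20% | 28.0% | 34.4% | 6.4 |
| One | 29.6% (usual care = 40%) | 40.0% | 48.3% | 8.3 |
| Two | 10% | 16.5% | 24.7% | 8.1 |
| Two | 15% | 24.1% | 35.3% | 11.2 |
| Two | 20% | 31.2% | 44.8% | 13.6 |
| Two | 26.6% (usual care = 40%) | 40.0% | 55.8% | 15.8 |

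**Milder contrast, 75% against 90%, two restarts.** At p = 15% it is 30.7% against 35.3%, or 4.6 points. At p = 20% it is 39.2% against 44.8%, or 5.6 points. With usual care at 40% (p = 20.5%) it is 40.0% against 45.7%, or 5.7 points. At p = 10% it falls to 3.4 points (21.3% against 24.7%). Equal shares give zero at any p.

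**Chance of declaring a difference when there is none in attendance.** Take ICC 0.05, inside the article's range of 0 to 0.15. The design effect is 1 + 225 × 0.05 = 12.25, and the effective number per arm is 8 × 226 / 12.25 = 147.6. For 40% against 55.8%, the standard error is √[(0.4 × 0.6 + 0.558 × 0.442)/147.6] = 0.0574. Then 0.158/0.0574 = 2.75, less the critical value 2.39, is 0.36, which gives about 64%. The same steps give about 17% for 40% against 48.3%, and about 8% for 40% against 45.7%. The nominal two-sided level is 1.7%. These use a normal approximation; a t reference with 14 degrees of freedom would lower them.

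**Does a fixed window remove it?** At p = 15%, a window of two months counts 1 − 0.85² = 27.8% in both arms, and one of three months counts 1 − 0.85³ = 38.6% in both, whatever visits were made.

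**The case against.** The definition is worded identically for all arms, and so is the trigger for the follow-up visit. The section on intervention and control separates the arms by the content and tools of the encounter, not by the number of visits. Getting CHWs to more unlinked people is also what a follow-up list is for, so linkage gained through extra visits may be a real effect of the strategy. No visit share is given anywhere, so every size above is conditional. All of this stands, and it limits the point. It does not remove it: a fixed window still credits every attendance that a visit brings about inside it, and removes only the credit for extra counting time.

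Four stronger readings are tempting and are not supported:

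- **Visits differ by arm by design.** The article does not say so. The follow-up list makes a difference plausible for TBCS-ST. It gives no reason for one between usual care and TBCS, since neither has the list.
- **Prompter visits lengthen the window.** They do not. Each visit opens one month whenever it occurs. Two visits d months apart (d below 1) overlap and give only 2 + d months in all, while a late visit moves the last eligible date out.
- **The Outcomes and Study participants sections contradict each other on which visit closes the window.** The wording is ambiguous. In the usual care description the CHW takes the first blood pressure, so the home test can be read as the first CHW contact. The second visit is then the follow-up visit, and the two texts agree.
- **A 20-point result would be mostly artefact.** That needs both two restarts and a wide gap in visit shares.

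**Conclusion.** The point holds in a conditional form. On the rule as written, the outcome on which the trial is powered has no common end date from home testing, and eligibility to count depends on receipt of a CHW visit. That much follows from the text alone.

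The size depends on visit delivery, which the article does not give. With 50% against 90% visited, it is about 4 to 6 points with one restart and 8 to 14 with two, for monthly linkage of 10% to 20%. With usual care at 40%, it is about 8 and 16 points. With 75% against 90% and two restarts, it is about 5 to 6 points (3.4 at the lowest monthly rate). With equal delivery it is zero. All of these assume a constant monthly linkage probability shared by both arms and no influence of the visit on attendance, so they isolate the counting component and do not forecast the trial's result. Set against planned steps of 20 points, the middle and upper part of the range is large enough to cloud interpretation.

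**What to change.** Define primary linkage in every arm as a confirmed dispensary visit within one fixed, pre-stated time from home-based testing, whatever CHW visits were made. The window should be long enough to cover the planned CHW follow-up and its one-month period. As the article sets no deadline for that visit, the trial team must choose and state the length: at least two months plus time to make the visit if there is one restart, and at least three if there are two. No change to the visit schedule is implied.

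Keep self-linked, CHW-mediated linked and chronic non-linked as descriptive categories. State in both the Study participants and Outcomes sections whether the home test counts as the first CHW visit.

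The cost is small. It is a change of wording, and the Trial status section says that the randomised part has not begun. The planning rates of 40%, 60% and 80% must be restated on the fixed window and the power statement checked against them.

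### Conditional logistic regression, in its standard form, does not give a valid arm comparison for the linkage co-primary when arm is assigned to whole community units

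*Protocol article*

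**What the plan says.** The Outcomes section of the protocol article names one method for the linkage co-primary: "We will compare the proportion linked to care between the three study arms using conditional logistic regression". It does not say what the regression conditions on or how standard errors are obtained.

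The section on the cluster randomized controlled trial fixes the design: "The unit of randomization will be the community unit". It adds: "Randomization will be stratified by division, so that the 9 units of Kosirai will be randomized separately from the 15 units of Turbo". The same section plans to compare baseline variables between the groups and to "make adjustments in our treatment effect estimates as needed using logistic regression adjustment", with no cluster term mentioned.

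The Statistical power section states that the study is powered on linkage, with an overall type I error of 5% and a Bonferroni correction over all pairwise comparisons. It does allow for clustering: "To account for cluster effects, we consider scenarios where intraclass correlation (ICC) ranges from 0 to 0.15". On cluster size it says: "It is expected that 226 people will be referred to the dispensary per community unit per year".

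Additional file 2, which is not shown, is cited only for the imputation of systolic blood pressure.

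**The concern.** The design and the power calculation both treat the community unit as the source of correlation. The analysis sentence does not, and the method it names fits poorly with assignment at unit level.

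Conditional logistic regression needs a conditioning set. The article describes two natural ones, the community unit and the division. The first removes the arm effect from the likelihood. The second respects the stratification but, with the standard errors that come with the method, counts everyone in a unit as independent.

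Linkage is the outcome on which the trial is powered, so the control of type I error promised in the power section depends on this sentence.

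**Working it through.** **Inputs.** From the article: 24 units (9 + 15), three arms, 226 people referred per unit, control linkage 40%, overall alpha 0.05 with Bonferroni over three pairs (0.05/3 = 0.0167 each), intraclass correlation (ICC) 0 to 0.15. Assumed: equal allocation (3 + 5 = 8 units per arm), equal unit sizes, two-sided tests and, in the simulations, beta-binomial variation between units.

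**1. The plan's own figure.** 5000 × 0.453 × 1/3 × 0.30 = 226.5, which reproduces the stated 226.

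**2. Conditioning on community unit.** In a unit with n people, y of them linked, all share the same arm coefficient β. The conditional likelihood contribution is exp(βy) divided by the sum of exp(βy) over all C(n, y) ways of choosing the y linked people. This equals 1/C(n, y), so β cancels. A numerical check on a simulated data set of 24 units agrees. The conditional log-likelihood is −243.70 at arm log odds ratios of (0, 0), (1, 2) and (−1, 3), and the score is zero apart from rounding. The arm effect is not estimable. None of the assumptions above is needed for this result.

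**3. Conditioning on division with model-based standard errors.** The design effect is DE = 1 + (226 − 1) × ICC, and the standard error is too small by a factor of √DE. With z = 2.394 for a two-sided 0.0167, the true rejection rate under the null is 2 × [1 − Φ(z/√DE)]. At ICC 0.05, for example, DE = 1 + 225 × 0.05 = 12.25, √DE = 3.5, 2.394/3.5 = 0.684, and the rejection rate is 0.494.

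The simulated columns come from 4000 null trials per ICC, with 40% linkage in every arm, analysed by logistic regression with a division indicator. With two very large strata this is practically the same as conditioning on division.

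| ICC | DE | √DE | Per comparison, formula | Per comparison, simulated | Family-wise, simulated |
|---|---|---|---|---|---|
| 0 | 1 | 1.0 | 0.017 | 0.017 | 0.04 |
| 0.01 | 3.25 | 1.8 | 0.184 | 0.175 | 0.37 |
| 0.05 | 12.25 | 3.5 | 0.494 | 0.496 | 0.77 |
| 0.10 | 23.5 | 4.8 | 0.621 | 0.614 | 0.87 |
| 0.15 | 34.75 | 5.9 | 0.685 | 0.687 | 0.92 |

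A separate simulation with the division-stratified Mantel-Haenszel score test gave 0.19, 0.49 and 0.69 per comparison and 0.39, 0.77 and 0.92 family-wise at ICC 0.01, 0.05 and 0.15. The family-wise figure at ICC 0.01 is therefore about 0.38.

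**4. An analysis that respects the unit.** In the same simulated trials, a linear comparison of unit-level proportions adjusted for division (24 units less 4 parameters, so 20 degrees of freedom) rejected in 0.014 to 0.018 of trials at nominal 0.0167, and in 0.047 to 0.053 at nominal 0.05, at every ICC tried from 0 to 0.15.

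**The case against.** A reader might infer that no reading of the sentence gives a valid test, or that the investigators plan to ignore clustering and are heading for a false claim of benefit. The document does not support either inference.

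- The article gives neither the conditioning set nor the variance estimator. Conditioning on division is a proper way to respect the stratification, and with a suitable cluster-robust variance or a permutation of units it would be valid. The word conditional is also sometimes used for cluster-specific, random-effects models. Nothing in the text excludes these.
- This is a condensed article, and the analysis plan is not shown. Degrees-of-freedom corrections and similar details are commonly left to that plan. The article is clearly aware of clustering, since it randomizes by unit and powers over a range of ICC values.
- The error rates belong to one reading only, division with naive standard errors. They are probabilities under the null, at scenario values of the ICC rather than estimates of it, and 0.15 is the top of the range. At 0 there is no inflation. The article itself expects large differences ("expected 60% linkage in the TBCS arm and 80% linkage in the TBCS-ST arm").

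All of this stands, and it limits what can be said about intent. It does not rescue the sentence. A method has been named, and in its ordinary meaning it does not suit the design. The only other analysis statement on this outcome, the logistic covariate adjustment, has no cluster term either. Nor can the point be carried over to systolic blood pressure, since the article names no regression model for that outcome.

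**Conclusion.** The point holds as a mismatch between a stated primary method and the design. It is not proof of which analysis was meant. The unit reading fails by algebra. The division reading fails if the method's own standard errors are used: type I error per comparison is about 0.18, 0.49 and 0.69 at ICC 0.01, 0.05 and 0.15 against 0.0167, and family-wise error is about 0.38, 0.77 and 0.92 against 0.05. Even the smallest of these family-wise rates is more than seven times nominal (0.38/0.05 = 7.6).

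The figures for the division reading rest on 8 equal units of 226 per arm, two-sided tests and naive standard errors. They fall away if a cluster-robust variance, a permutation of units or a random-effects model was intended, and the article states none of these. Because linkage is the outcome on which the study is powered, the sentence should be corrected before the trial starts.

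**What to change.** Replace the sentence in the Outcomes section with an analysis that accounts for community unit. One possible wording: *Linkage will be compared between arms with a mixed-effects logistic model that has arm and division as fixed effects and a random intercept for community unit, with a small-sample correction suited to 24 clusters.* A cluster-level analysis stratified by division would serve equally well. If a random-effects model, a cluster-robust variance or a permutation of units was intended all along, saying so settles the matter.

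Apply the same cluster handling to the covariate-adjusted logistic analysis described in the section on the cluster randomized controlled trial.

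The cost is a change of wording in two places, with no new data. Confidence intervals will be wider than under the naive analysis, but correct, and the power calculation already allows for clustering. The Trial status section says that the cluster trial has not begun, so the change can be made before any outcome data exist.
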